## Abstract

**Background:**

Although pain after back surgery is known to be difficult to control, various treatment options are available to patients and physicians. A protocol for a confirmatory randomized controlled trial (RCT) on pain and function after back surgery was designed based on the results of a pilot trial. The aim of this study is to compare the effectiveness and safety of electroacupuncture (EA) with usual care (UC) versus UC alone on pain control and functional improvement after back surgery.

**Methods/design:**

This study is a multi-center, randomized, assessor-blinded trial with an active control conducted in conjunction with a cost-effectiveness analysis and qualitative research. Participants with non-acute low back pain with or without leg pain after back surgery who have a Visual Analogue Scale (VAS) pain intensity score ≥ 50 mm will be randomly assigned to either the EA with UC group (n = 54) or the UC group (n = 54). Following randomization, participants in both groups will receive the same UC treatment twice a week for a four-week treatment period. Participants assigned to the EA with UC group will additionally receive EA twice a week for the same four-week period. The primary outcome measure will be assessed using a VAS pain intensity score for low back pain. The secondary outcomes will include the Oswestry Disability Index, EuroQol 5-Dimension score, and drug intake. The primary and secondary outcomes will be measured at one, four, and eight weeks post randomization.

**Discussion:**

The results of this study will provide evidence of the effectiveness and cost-effectiveness of EA in managing postoperative pain following back surgery. In addition, the qualitative research results will help improve the quality of integrative medical interventions.

**Trial registration:**

Clinical Research Information Service (CRIS), Republic of Korea, KCT0001939. Registered on 8 June 2016.

**Electronic supplementary material:**

The online version of this article (10.1186/s13063-018-2461-6) contains supplementary material, which is available to authorized users.

## Background

Low back pain (LBP), a widespread condition, has a high global prevalence of 10% [1]. According to the Global Burden of Disease 2010 Study, LBP is the sixth highest overall burden on the society of the 291 conditions [2] and has thus been the focus of a number of related studies [3]. Although acute LBP is usually recovered within six weeks [4], the clinical guidelines recommend surgery such as spinal fusion for chronic LBP in failure of more than two years of all other recommended conservative treatments [5]. While lumbar spine surgery methods such as discectomy and spinal fusion continue to increase in popularity, [6] various complications may occur following back surgery, possibly resulting in worse conditions [7].

The most common complication associated with back surgery is pain and approximately 40% of patients may experience pain after lumbar spine surgery [8]. Therefore, in cases in which pain persists after back surgery, pain management is essential [9, 10]. Opioid analgesic drugs are a cornerstone of postoperative pain management [11]. However, opioids may cause various side effects ranging from itching and sedation to nausea [12]; effective and safe pain management after back surgery is thus warranted.

Several clinical trials have demonstrated that acupuncture is generally safer [13, 14] and more cost-effective [15, 16] than routine care. A recent systematic review suggested that certain modes of acupuncture improved acute postoperative pain and reduced opioid use [17]. Recently, the clinical practice guidelines from the American College of Physicians in 2017 indicated that acupuncture improved pain in acute and chronic LBP [18].

Electroacupuncture (EA) is the application of electrical stimulation to acupuncture techniques. Currently, EA is a common treatment for pain management [19, 20], including myofascial pain [21], osteoarthritis of the knee [22], chronic shoulder and neck pain [23], and LBP [24]. EA is regarded to modulate pain through significant changes in bioactive chemicals such as opioids, serotonin, and norepinephrine in peripheral injury sites, the spinal cord, and supraspinal structures [20].

In our recent systematic review, we found that acupuncture analgesia for pain after back surgery yields positive results [25], but there have been few clinical trials that have reported the effectiveness of EA for pain following back surgery. Therefore, we conducted a pilot randomized controlled trial (RCT) of EA in patients with non-acute pain after back surgery between 2013 and 2014 to assess the feasibility of a full-scale study and to calculate an adequately powered sample size [26]. Using the pilot RCT results (currently being prepared for submission to a peer-reviewed journal), we calculated the sample size and tested the acceptability of the study design to assess the effectiveness and safety of EA for post-back surgery pain. We thus propose a pragmatic, confirmative, and comparative multi-center RCT design following the CONSORT [27] reporting guidelines and Standards for Reporting Interventions in Clinical Trials of Acupuncture (STRICTA) recommendations [28]. We selected usual care as the comparator in this study to reflect real-world conditions with reference to the most common treatments used in patients with LBP as assessed from the 2011 Korean Health Insurance Review and Assessment (HIRA) statistics [29] or clinical practice guidelines [30]. This study will additionally include a cost-effectiveness analysis and qualitative research.

## Methods/design

### Objective

We hypothesize that EA may have better effectiveness and cost-effectiveness with good tolerance in safety in patients with pain after back surgery when used as complementary treatment with UC. The aim of this study is to compare the effectiveness and safety of EA with UC versus UC alone on pain control and functional improvement after back surgery. Additionally, cost-effectiveness analyses will be conducted to investigate the effectiveness and/or cost-effectiveness of EA in patients with pain after back surgery; qualitative research will be conducted to understand participants’ personal experiences with symptoms, factors influencing their pain, and their perceptions of the intervention.

### Design

This study is a multi-center, randomized, assessor-blinded trial with two parallel arms and an active control. This study will be conducted in three hospitals in South Korea. Participants will be independently recruited at each hospital site through online advertisements placed on the hospital website and offline on-site advertisements, such as hospital bulletin boards, to obtain the appropriate participant enrollment and target sample size. Potential participants will be required to undergo screening to determine their eligibility. When eligible, participants will be asked to provide written informed consent, after which the baseline evaluation will be conducted by a study researcher. At screening, a clinical research coordinator (CRC) will collect information on various basic sociodemographic characteristics such as gender, age, vital signs, height, weight, and medication history. Korean medicine doctors (KMDs) will collect information on the medical history of individuals who have received spinal surgery, such as the timing of surgery, type of surgery (i.e. fusion, decompression, or discectomy), surgically involved vertebra(e), number of surgeries, time of pain, onset of symptoms, and duration of symptoms. On their second visit, screened participants who are considered eligible for trial participation based on the inclusion and exclusion criteria will be randomly allocated using a 1:1 ratio to either the EA plus UC group or the UC alone group. After randomization, the treatment procedure will be scheduled and managed by a CRC. To maximize participant retention, there will be flexibility during the visit period and researchers will allow actual visits to be within seven days of prescheduled visits. The post-treatment follow-up will occur one, four, and eight weeks following the four-week interventional period to know whether the treatments effects are maintained.

All participants will be enrolled through voluntary participation and written informed consent from all participants will be obtained in accordance with the Declaration of Helsinki [31]. Trial participation may be terminated at any time during the trial through voluntary refusal to continue or in cases of significant clinical deterioration as judged by KMDs. Participants suffering from trial-related problems or adverse events (AEs) may receive medical treatment for compensation. The trial will be insured to compensate for any AEs related to the trial interventions. This study is registered at the Korea National Institutes of Health Clinical Trials Registry, “Clinical Research Information Service (https://cris.nih.go.kr/cris/en/).” It is also included in the WHO Registry Network (registry number KCT0001939). The study flow chart is presented in Fig. 1 and the trial timetable is depicted in Fig. 2.

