### Blinding

As the practitioners and participants in this trial cannot be blinded to the allocation of treatment groups due to the differences in the nature of the EA intervention, only the outcome assessor will be blinded. Outcome assessors will not participate in the EA or UC treatment, and they will conduct the outcome assessments in a separate room without any knowledge of participant allocation and are therefore considered safe from detection bias [32]. Unblinding the assessors will be permissible only in specific situations, such as when knowledge of the actual treatment is highly necessary for the appropriate management of participants (e.g. serious AEs (SAEs).

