### Education on standardization of study procedures

First, we will develop standard operating procedures (SOPs) for the entire trial, interventions, roles, and training of assessors, researchers, and CRCs through a consensus based on experience with the previous pilot trial [26]. All researchers will be required to complete a clinical trial training in accordance with their individual roles. Licensed KMDs will be involved in this trial as practitioners or outcome assessors. Specifically, practitioners will have had three or more years of clinical experience after being certified with KMD licensure by the Korean Ministry of Health and Welfare. They will have undergone an educational course to standardize the study procedures and this process will ensure that they adhere to the study protocol and are familiar with the study interventions and their administration. All of the practitioners involved in the trial will undergo intensive training customized by role (two training sessions of a 1-h duration or more, with each session including lectures and hands-on sessions) to enable full comprehension of the EA procedure, which is semi-standardized regarding acupoints, needling depth, and manual stimulation methods. The study details, protocol, and outcome assessment process will additionally be standardized among outcome assessors through trainings based on the SOPs.

In this study, to improve the adherence to protocol, the researchers will be trained on the SOPs and regularly monitored. The participants will be thoroughly explained on the process of the study, noticed of their visit schedules via phone calls or text messages, and provided financial compensation to ensure their adherence to the protocol.

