### Outcome measurements

#### Primary outcome

The primary outcome of this study is the pain intensity of LBP after back surgery as assessed by a VAS. Post-surgical LBP severity will be quantified using a VAS pain intensity score as determined on a 100-mm horizontal line, where 0 indicates no pain and 100 indicates intolerable pain [35, 36]. The level of back pain during the previous week will be assessed using a 100-mm pain VAS at baseline (visit 2), before each treatment session (visits 2–9), and at each post-treatment follow-up visit (visits 10–12); the primary endpoint will be VAS pain intensity score at visit 10, representing treatment completion. The outcome measures will be assessed before treatment at each visit to ascertain the effectiveness of the previous treatment(s).

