### Adverse events

Any AEs will be monitored and reported by the researchers at each visit. All expected and unexpected AEs potentially related to the study will be monitored and their progress will be recorded until resolved. The physicians will decide whether trial participation should be discontinued based on these reports.

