### Sample size

An appropriately powered full-scale sample size has been estimated using the mean between-group difference in the primary endpoint (VAS pain intensity score for LBP) identified in the previous pilot study. Based on intention-to-treat (ITT) analysis, the mean difference and standard deviation (SD) in the VAS pain intensity score for LBP between the EA plus UC group and UC alone group is estimated to be 14.02 mm ± 22.12 mm. Although this reduction in pain intensity is not moderately clinically meaningful, it does represent a minimally important difference [41].

The total number of individuals required per group is 40, considering a two-tailed test with 80% test power and a 5% significance level. After accounting for a 25% drop-out rate and the 1:1 allocation ratio, the final sample size per group has been calculated to be 54, resulting in a total sample size estimate of 108 for a full power analysis.

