### Statistical analysis

The statistical analysis will be conducted using both the ITT and per-protocol (PP) analysis principles in parallel. Multiple imputation methods will be used for missing data in the ITT analysis. A PP analysis will be performed as a secondary analysis excluding data from drop-outs for any reason. An interim analysis will not be performed. An independent t-test or Wilcoxon rank sum test will be used to analyze continuous data to test for significance in between-group differences and will be presented as the mean ± SD. Chi-square test or Fisher’s exact test will be conducted for categorical data and the data will be described as the frequency and percentage (%). To analyze the VAS pain intensity score as the primary outcome, we will perform an analysis of covariance (ANCOVA) considering the baseline scores as covariates and treatment group as the fixed factor. A paired t-test or Wilcoxon signed rank test will be performed to analyze within-group differences pre and post treatment. Repeated measure analysis of variance (RMANOVA) will be used to analyze the between-group differences at each visit. Subgroup analysis will be conducted according to age, gender, and medical history (e.g. the existence of osteoporosis, pre-surgery diagnoses), which may have the possibility of affecting the treatment effects on each outcome.

A safety assessment will be performed for all AEs occurring during the study period. The incidence of AEs, AEs leading to withdrawal, and SAEs will be summarized by group and analyzed using Fisher’s exact test or chi-square test.

All statistical analyses will be conducted by a designated statistician blinded to group allocation with SAS® Version 9.4 (SAS institute Inc., Cary, NC, USA) for Windows. The level of significance will be set at 5%.

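### Clinicians may end trial participation, not only treatment, for deterioration or adverse events, and nothing in the article keeps these participants in outcome assessment

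*Protocol article*

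**What the plan says.** Two rules let clinicians take a participant out of the trial. In Design: "Trial participation may be terminated at any time during the trial through voluntary refusal to continue or in cases of significant clinical deterioration". The same sentence leaves the judgement of deterioration to KMDs. In Adverse events: "The physicians will decide whether trial participation should be discontinued based on these reports". Both speak of trial participation. Neither separates stopping treatment from leaving the study.

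On who decides, Blinding states that "only the outcome assessor will be blinded". The section on standardization of study procedures adds: "Licensed KMDs will be involved in this trial as practitioners or outcome assessors". The article does not say which of these KMDs, or which physicians, take the removal decision.

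On the outcome, Primary outcome states that "the primary endpoint will be VAS pain intensity score at visit 10, representing treatment completion". The VAS is also recorded at baseline and before every treatment session (visits 2–9).

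On analysis, Statistical analysis states: "Multiple imputation methods will be used for missing data in the ITT analysis". The PP analysis leaves out drop-outs whatever the reason. The sample size was set "After accounting for a 25% drop-out rate".

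**The concern.** An ITT comparison aims at the outcomes of everyone randomized, including those who do badly. This matters all the more here, because the trial is described as pragmatic and as measuring effectiveness under real-world conditions. Read as written, the removal rules allow a participant to leave the trial because of worsening, and in a back-pain trial worsening is closely tied to the primary endpoint. The participant's visit-10 VAS is then a modelled value in the ITT analysis and absent from the PP analysis, so neither analysis observes it.

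Participants and practitioners know the allocation, and the article gives no criterion for what counts as significant deterioration. The rate of removal could therefore differ between arms. If removed participants are in truth worse than their imputed values, unequal removal shifts the primary contrast. The same gap reaches the ODI, the EQ-5D and the economic evaluation, which is also analysed by ITT with multiple imputation.

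**Working it through.** **1. The plan's own figure.** Inputs from Sample size: difference 14.02 mm, SD 22.12 mm, two-sided 5% level, 80% power, 25% drop-out.

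- n per group = 2 × (1.960 + 0.842)² × 22.12² / 14.02² ≈ 39.1, rounded up to 40.
- Allowing for drop-out: 40 / 0.75 = 53.3, rounded up to 54 per group, 108 in total.

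Both figures reproduce, so there is no arithmetic error.

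**2. How many endpoint values may be imputed.** The allowance is 0.25 × 108 = 27 participants, or 54 − 40 = 14 per group. It covers drop-out for all causes. The article does not say what share would be removal for deterioration or adverse events.

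**3. What happens to a removed participant.**

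| Step | Section | Consequence |
|---|---|---|
| Participation ended | Design; Adverse events | No provision for later outcome visits |
| Endpoint at visit 10 | Primary outcome | No value if removed earlier |
| ITT analysis | Statistical analysis | Value imputed |
| PP analysis | Statistical analysis | Participant excluded |
| AE follow-up to resolution | Adverse events | Continues, but does not cover VAS, ODI or EQ-5D |

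**4. Illustrative bias.** Let f be the share removed in an arm. Let D be how much worse, in mm, the true visit-10 VAS of removed participants is than the imputed value, after the imputation has used their earlier scores. Each arm mean is then understated by f × D. With the same D in both arms, the size of the shift in the group difference is |f₁ − f₂| × D. All values of f and D below are assumptions; none is in the document.

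| Removed, one arm v other | D (mm) | Shift (mm) | Share of 14.02 mm |
|---|---|---|---|
| Equal | any | 0 | 0% |
| 10% v 5% | 20 | 0.05 × 20 = 1.0 | 7% |
| 15% v 5% | 10 to 30 | 0.10 × D = 1.0 to 3.0 | 7% to 21% |
| 20% v 5% | 30 | 0.15 × 30 = 4.5 | 32% |
| 25% v 10% | 10 to 30 | 0.15 × D = 1.5 to 4.5 | 11% to 32% |

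If usual care loses more of these participants, the benefit of electroacupuncture is understated. If the electroacupuncture arm loses more, it is overstated. If D is zero, there is no bias at any removal rate.

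**5. What fuller follow-up would gain.** With 40 observed per group, power by the t-test is 79.9%. With all 54 observed it would be 90.4% (normal approximation 80.9% and 90.9%). This is an upper limit: it assumes nobody is lost and that the 14.02 mm difference still holds when participants who stopped treatment are counted.

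**The case against.** **The article condenses a fuller document.** The Design rule stands among statements on consent, compensation and insurance. It says participation may be ended, and it does not say that measurement stops. Handling of data after discontinuation could be in the full protocol or the standard operating procedures. This part stands as a caution: a reader might infer that the worst outcomes will certainly go uncollected, and the text does not establish that. But the point rests on what the rules say, which is that trial participation ends. If the full protocol keeps these participants in follow-up, the published wording misstates it and should be brought into line.

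**The decision-makers need not be unblinded.** A reader might infer that unblinded clinicians make the removals. The documents name only KMDs and physicians, and some KMDs are blinded assessors. What can be said is narrower: the decision is not reserved for a blinded person, and treating practitioners are not blinded.

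**Multiple imputation may cope.** This is the strongest objection. With VAS scores from visits 2–9, a worsening participant often has that worsening on record. If removal depends only on recorded scores and the imputation model uses them, the missing values are plausibly missing at random and D is near zero. It would be wrong to say that imputation cannot repair the loss. What remains is the part of removal that recorded scores do not explain, such as worsening after the last score, clinical signs that the VAS does not capture, or removal after only a few visits.

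**The size is assumed.** This is correct. The top of the range is demanding: 30 mm exceeds the planning SD of 22.12 mm, and 25% in one arm would use the whole all-cause allowance on these removals alone.

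**Retention measures exist.** The seven-day visit window, reminders and financial compensation help against voluntary loss. They do not act on removal by a clinician. Enlarging the sample from 40 to 54 per group protects precision but not against bias.

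**Conclusion.** The point holds as a weakness in a stated rule, not as a demonstrated bias. As written, participants can be taken out of the trial for reasons linked to the primary endpoint, no blinded decision is required, and no later outcome measurement is provided for. The primary contrast may be biased to the extent that the VAS from visits 2–9 does not explain removal. The direction cannot be known from the document. The illustrative size is 1 to 4.5 mm, or 7% to 32% of 14.02 mm. It rests wholly on assumed removal rates and gaps, and is zero if removal and gap are equal in both arms or if imputation recovers the missing values. The Sample size section itself describes 14.02 mm as a minimally important rather than a moderately meaningful difference, so a shift of a few millimetres could change how the result is read. The change is worth making because it costs little.

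**What to change.** Leave the clinical decision to stop treatment, and who takes it, as it is. Change what follows from it.

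- **Wording.** In Design and in Adverse events, state that such a decision ends study treatment only. Leaving the study requires withdrawal of consent.
- **Follow-up.** Unless consent is withdrawn, collect VAS and ODI at visits 10–12 and EQ-5D at visits 10–13, and use these values in the ITT analysis. The VAS is marked on a 100-mm line, so it has to be taken in person or on a posted form. Telephone contact is suitable for the EQ-5D, for which the article already plans it at visit 13.
- **Imputation.** For values still missing, include the VAS from visits 2–9 in the imputation model.
- **Sensitivity analysis.** Add a missing-not-at-random analysis in which imputed values are worsened by a delta that may differ between arms, for example across the 10 to 30 mm used above.
- **Record.** Add a case report form field that separates treatment stopped from study stopped, with the reason.

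The cost is a short amendment to a trial already recruiting, one form field and a few extra follow-up contacts. Outcomes of participants who left before the amendment may not be recoverable, which is a further reason for the sensitivity analysis.
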